**Table 2: Primary and Secondary Outcome Measures**

## 5.

The primary outcome for the new phase of the study will be the feasibility and acceptance of HBPM by families of children with one elevated BP measurement. We will measure feasibility of HBPM by investigating 1) the percent of patients who were not interested in receiving the HBPM device, 2) the percent of patients who did not return any data on the HBPM measurements, 3) the percent of patients completing all requested measurements and the percent completing at least half

of the requested measurements, 4) the days between agreeing to come in for the device, to when they received the HBPM and when data was returned (actual dates will only be visible to the Honest Broker), and 4) the concordance between HBPM, and manual in-clinic BP measurements, and 5) percent of children diagnosed with hypertension. For those patients contacted for HBPM, we will continue to track the above pre-COVID outcomes as well. No data described above will be collected on patients not identified for this new phase of the study at this time.

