We will ask 9 already enrolled clinics if they are willing to participate in this new phase of the study. We will only study patients at 6 clinics, but because of the challenges of retaining sites during this pandemic, each clinic will be paired with another clinic at their site as a back-up. All clinics will be chosen from the 9 Montefiore Medical Group clinics that previously enrolled, allowing us to centralize the process for outreach and resulting). Sites will be given lists of 100 patients with one prior elevated BP measurement who were already included in data entered during the first phase of BP-CATCH (600 patients total). These patients will be 3 to 22 years old as this is the population to which the pediatric hypertension guidelines apply. The research coordinator will contact these 100 patients from each site and for 18-22 year olds, obtain verbal phone consent. For 7-17 year olds we will ask the caregiver to obtain verbal assent for participation. For 3-6 year olds, the caregiver will provide verbal consent. As our research assistant only speaks English, only English speaking participants will be enrolled in the study. Due to lower enrollment, we are increasing the number of patients we are calling from 50 to 100 and increasing from 5 to 6 sites. Each patient and caregiver will be requested to return to clinic to obtain a HBPM with an appropriately sized cuff based on arm circumference measurements, receive education on its use and instruction on how to record three morning and three evening blood pressures for seven days. In addition, each patient will undergo manual BP measurements to correlate with the BPs obtained by HBPM. This is a crucial and guideline based next clinical step, regardless of this study. We anticipate approximately 40 patients from each site will return to clinic to obtain the device (200 patients total). The study research coordinator will call patients one week later and ask for the BP measurements and ensure this information is sent to the appropriate clinician. We anticipate at least 20 patients from each site will return these data (100 patients total). These measurements will be entered into REDCap confidentially, along with dates of visit and measurements return. This will allow us to investigate the feasibility of HBPM as well as the correlation of HBPM with manual in-clinic BP measurements. Dates will be seen only by the REDCap "honest broker" and scrubbed from the database before being provided to the research team.

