For the 100 patients already identified by the study site as having an elevated BP measurement but no follow-up, data identified above will be collected. We will also collect data on manual in-clinic BP measurements, HBPM data, time between phone contact, receiving HBPM and returning data and ABPM data and nephrology follow-up data. All these data will be de-identified as described above and verbal phone consent will be obtained from caregivers and adult patients, and verbal assent will be obtained by the parent for children 7-17 years old. It is impractical for the study's one research assistant to be present at all 200 anticipated patient visits across 6 clinical sites to obtain in-person consent. Additionally, in the face of the COVID pandemic and the need to maintain social distancing, all MMG sites have restricted access to non-clinical research staff, especially in cases where consent and research processes can be conducted over the phone. Performing verbal consent will be safer for participants, the research assistant, and MMG staff in the involved sites. Additionally, it is challenging to obtain verbal assent from 7-17 year olds while on the phone, so we will ask the caregivers to perform that task under the research assistant's guidance. Paper versions of the completed consent form will be mailed to all participants. Providers and patients will be free to refuse to collect these data, refuse to receive the HBPM or the ABPM, or refuse to return to clinic as per normal care. See attached data collection form.

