**EXCLUDE Patients:** with repeat blood pressure measurements visit since last BP-CATCH visit.**H. Office**

1. How many attempts did the clinic make before getting in touch with the patient's caregiver (e.g. parent)?

☐ 1 ☐ 2 ☐ 3 ☐ 4 ☐ 5 ☐ 62. Was clinic able to get in touch with patient's caregiver (e.g. parent)? ☐ Yes ☐ No **IF NO, STOP COMPLETING FORM**

3. Was caregiver interested in bringing patient to clinic for repeat BP measurements?

☐ Yes ☐ No **IF NO, STOP COMPLETING FORM**

4. Date of Clinic Visit: \_\_/\_\_/\_\_\_\_

5. Patient age (in years) at this visit: \_\_\_\_\_ years (round to nearest 0.5 year)

6. Height **at this visit with an elevated blood pressure** \_\_\_\_\_ (centimeters) ☐ Not done at this visit7. Weight **at this visit with an elevated blood pressure** \_\_\_\_\_ (kilograms) ☐ Not done at this visit**I. Office Manual Blood Pressure (BP) Measurements****1. First manual BPs results**

1a. Systolic Blood Pressure: \_\_\_\_\_

1b. Diastolic Blood Pressure: \_\_\_\_\_

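### The home-monitoring feasibility interval starts at agreement or phone contact, but the BP-CATCH 2.0 form records neither date, so the intervals from that start cannot be derived from it

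*Protocol*

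**What the plan says.** Section 5 (the paragraph after Table 2) makes feasibility and acceptance of HBPM the primary outcome of the new phase and lists several components. The first of the two items numbered 4 is "the days between agreeing to come in for the device, to when they received the HBPM and when data was returned".

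The Data and Safety Monitoring Plan, describing what will be collected for this phase, names "time between phone contact, receiving HBPM and returning data" and closes with "See attached data collection form".

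Section 3, on what is entered into REDCap, mentions the measurements "along with dates of visit and measurements return". It adds that dates are visible only to the honest broker and are removed before the research team receives the data.

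The attached form for this phase is the BP-CATCH 2.0 Chart Review Tool. Section H opens with three undated items: a count of call attempts (H1), a yes/no on whether the caregiver was reached (H2), and a yes/no item, "Was caregiver interested in bringing patient to clinic for repeat BP measurements" (H3). Next comes the first dated step, "4. Date of Clinic Visit". Section J then records the date the device was received (J1) and the date the clinic received the readings (J4a).

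**The concern.** A time interval needs a recorded start and a recorded end. The protocol fixes the end points and the form captures both of them, but the start is nowhere on the instrument that the text relies on. The two passages also differ on what the start is: agreement in Section 5, phone contact in the Data and Safety Monitoring Plan. The form allows up to six call attempts, so the two need not fall on the same day, and phone contact could itself mean the first attempt or the first successful one.

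At stake is one named component of the phase's primary outcome: how long it takes a family that has said yes to obtain the device. A statistical analysis plan can define an interval, but it cannot recover a date that nobody wrote down. The gap therefore has to be closed at data capture.

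**Working it through.** No published figure is being reproduced here. The check sets the measure's start and end points against every date field on the form.

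**Date fields on the BP-CATCH 2.0 form**
- Patient information: date of birth (clinic use only, not entered into REDCap).
- Section H: clinic visit (H4).
- Section J: device received (J1), device first used (J2), the date beside each morning and evening set of readings, data received by the clinic (J4a).
- Section K: ambulatory monitor picked up, nephrology visit, ambulatory monitor started, ambulatory monitor returned, summary page emailed.

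None of these is a date of contact or of agreement. The form runs unbroken from its title to its closing line, so the gap is not explained by removed pages. The first-phase chart review tool has no such field either.

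**Intervals the measure needs**

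| Interval | Start on form | End on form | Derivable? |
|---|---|---|---|
| Agreement or contact to device received | none | J1 | No |
| Agreement or contact to data returned | none | J4a | No |
| Device received to data returned | J1 | J4a | Yes, J4a − J1 |

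Section 5 can be read as asking for the first and third rows, or for the first and second. On the first reading one of the two intervals is lost; on the second, both are.

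**Could the clinic visit date stand in for the start?** No. Under Section 3 the family returns to the clinic to collect the device, so H4 and J1 normally fall on the same day. The wait in question is over by H4.

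**Who is affected?** Everyone who receives a device. Section 3 puts that at 200 patients in total; its own figure of about 40 at each of 6 sites would give 6 × 40 = 240. On either count the interval from agreement or contact is missing for all of them.

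**What is not affected?** The percentages not interested, returning no data, and completing all or at least half of the readings; the concordance with manual measurements; and the percentage diagnosed. None of these uses the missing date.

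**The case against.** The strongest reply is that the form need not be the only source. One research coordinator calls all 600 patients and obtains verbal consent by phone, and a completed consent form is mailed to each participant. A dated consent record may well exist. That stands: a reader might infer that the study does not hold the date at all, and the documents do not show this, because the consent pages were removed. But no visible text sends such a date to REDCap or ties it to this measure, and Section 3 names only visit and return dates.

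Other stronger readings are tempting and should not be drawn:

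- *That the interval would come out near zero and make the pathway look immediate.* This would follow only if an analyst used the clinic visit as the start, which the protocol nowhere proposes. Followed as written, the interval is missing, and a missing value is visible to the analyst.
- *That families who agree but never come are lost.* Those with yes at H3 and no visit date at H4 can be identified and counted. Only their elapsed time is unavailable, and the measure is worded as running to receipt of the device.
- *That the first-year figure of over 75% not returning on time shows how large this wait is.* That figure (Section 1.2) concerns return for second or third office measurements. It is not a wait after agreeing to collect a device.
- *That a censored time-to-event analysis is required.* The phase is a pilot with descriptive reporting, and that analysis is optional.

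It is also fair to say that Aim 4 lists acceptance, completion, return and correlation, not waiting time. The interval is one component among several.

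**Conclusion.** The mismatch is real and limited. The intervals starting at agreement or phone contact, which Section 5 and the Data and Safety Monitoring Plan both promise, cannot be derived from the form that the latter points to. Those two places also disagree on the start point. The loss covers all device recipients for those intervals and nothing else in the feasibility outcome. How long the missing wait is cannot be estimated from the documents.

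The conclusion rests on two assumptions: that the BP-CATCH 2.0 tool is the attached form meant for this phase, and that no other record supplies the date to the study database. If the coordinator's consent log is dated and can be linked, the data are recoverable and what remains is a documentation gap.

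**What to change.** 1. Choose one start point, agreement to come in or phone contact, and word it identically in Section 5 and the Data and Safety Monitoring Plan. If phone contact is chosen, say whether it means the first attempt or the first successful call.
2. Add a dated field for that event to Section H after H3, and add it to the dates that Section 3 lists for REDCap. The honest broker passes it on as days elapsed only.
3. For patients already called, link the coordinator's verbal-consent date if it is held. If it is not, state that the interval is unavailable for them.
4. Report the interval among those who received the device, with the number who agreed but did not attend shown beside it.

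The cost is one date field, completed during a call that the coordinator already makes, plus a small wording change. No new contact with families is needed.

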*Hypothesis 3: Practices randomized to a HTN QIC with a hub and spoke model, following participation in the two QICs described above, will experience an additional 15% reduction in pediatric HTN and EBP diagnosis and management errors as compared to QICs with HTN subspecialist involvement but no focus on hub and spoke co-diagnosis and co-management.*

Given the impact of COVID-19 on pediatric care across the country, the number of in-person pediatric visits has declined sharply. Many sites are now overwhelmed by changes to practice patterns due to COVID-19, and are being asked to see patients virtually. In this environment it is no longer feasible to run a QIC that relies on in-person pediatric BP measurements. For this reason, we paused the study on March 24, 2020. In discussions with our funder, AHRQ, and to continue this quality improvement work, we have created a modified aim as below:

Specific Aim 4: Determine whether it is feasible for families of children with one elevated blood pressure measurement to 1) accept home blood pressure monitoring (HBPM), 2) complete HBPM measurements, 3) return HBPM measurement data to clinicians, and 4) the correlation of these data with in-office manual BP measurements.

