**2. Second manual BPs results**

2a. Systolic Blood Pressure: \_\_\_\_\_

2b. Diastolic Blood Pressure: \_\_\_\_\_

3. Was teaching on Home Blood Pressure Monitor (HBPM) done by Clinic?

☐ Yes ☐ No**J. Home Blood Pressure Measurements**

1. Date Patient received HBPM (MM/DD/YYYY): \_\_/\_\_/\_\_\_\_

2. Date Patient started using HBPM (MM/DD/YYYY): \_\_/\_\_/\_\_\_\_

|                      | Date | BP Reading # 1
(mmHg) |                  | BP Reading # 2
(mmHg) |                  | BP Reading # 3
(mmHg) |                  |
|----------------------|-------------|--------------------------|------------------|--------------------------|------------------|--------------------------|------------------|
|                      |             | Systolic          | Diastolic | Systolic          | Diastolic | Systolic          | Diastolic |
| Day 1 Morning | / /         |                          |                  |                          |                  |                          |                  |
| Day 1 Evening | / /         |                          |                  |                          |                  |                          |                  |
| Day 2 Morning | / /         |                          |                  |                          |                  |                          |                  |
| Day 2 Evening | / /         |                          |                  |                          |                  |                          |                  |

|                      |   |   |  |  |  |  |  |  |
|----------------------|---|---|--|--|--|--|--|--|
| Day 3 Morning | / | / |  |  |  |  |  |  |
| Day 3 Evening | / | / |  |  |  |  |  |  |
| Day 4 Morning | / | / |  |  |  |  |  |  |
| Day 4 Evening | / | / |  |  |  |  |  |  |
| Day 5 Morning | / | / |  |  |  |  |  |  |
| Day 5 Evening | / | / |  |  |  |  |  |  |
| Day 6 Morning | / | / |  |  |  |  |  |  |
| Day 6 Evening | / | / |  |  |  |  |  |  |
| Day 7 Morning | / | / |  |  |  |  |  |  |
| Day 7 Evening | / | / |  |  |  |  |  |  |

4. Did the Clinic received the HBPM data from Patient?

☐ Yes ☐ No

4a. If yes to the above question, what date did the Clinic received the HBPM data? \_\_/\_\_/----

5. Was Provider notified of HBPM readings?

☐ Yes ☐ No

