#### K. Ambulatory Blood Pressure Monitor (ABPM)

1. Based on HBPM and Manual BP Measurements, did the patient meet the criteria to receive an ABPM and receive a nephrology referral? \*ABPM given if patient had discordant hypertension stages (e.g. normal, elevated, Stage 1 or Stage 2) between HBPM and manual BP measurements and 8 or older, all discordant patients receive nephrology referral

☐ Yes ☐ No **[STOP COMPLETING FORM]**

2. Was caregiver interested in receiving an ABPM and nephrology referral?

☐ Yes ☐ No **IF NO, STOP COMPLETING FORM**

3. Date Patient picked up ABPM (MM/DD/YYYY): \_\_/\_\_/\_\_\_\_ or ☐ N/A because patient <8 years old

4. Date Patient came for nephrology referral (MM/DD/YYYY): \_\_/\_\_/\_\_\_\_

or ☐ Not interested in nephrology referral ☐ Did not need nephrology referral

5. Date Patient started ABPM (MM/DD/YYYY): \_\_/\_\_/\_\_\_\_

6. Date Patient returned ABPM (MM/DD/YYYY): \_\_/\_\_/\_\_\_\_

7. Date ABPM summary page(s) scanned and emailed to PK and Provider: \_\_/\_\_/\_\_\_\_

8. Final diagnosis per ABPM and nephrology: \_\_\_\_\_

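### The home-monitoring form gives only some children a field for a diagnosis, so the diagnosed percentage would be undercounted by an amount the Protocol does not let one estimate

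*Protocol*

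**What the plan says.** Protocol section 5, in the paragraph on the new phase, makes feasibility and acceptance of HBPM the primary outcome and lists its measures. The first is "the percent of patients who were not interested in receiving the HBPM device"; the last is "percent of children diagnosed with hypertension". Neither is restricted to a subgroup. The same paragraph says the earlier outcomes will still be followed for the patients contacted.

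The instrument for this phase is the BP-CATCH 2.0 Chart Review Tool in the appendix.

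- **H3**, the only question about interest before a device is issued, reads "Was caregiver interested in bringing patient to clinic for repeat BP measurements". An answer of No ends the form.
- **K1** asks "did the patient meet the criteria to receive an ABPM and receive a nephrology referral". Its note explains who qualifies: "ABPM given if patient had discordant hypertension stages", with an age limit, and all discordant patients are referred. An answer of No ends the form.
- **K2** asks whether the caregiver wants the ambulatory monitor and the referral. An answer of No ends the form.
- **K8**, the last item and the only diagnosis field, is "Final diagnosis per ABPM and nephrology".

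The earlier BP-CATCH Chart Review Tool has diagnosis items in Section D (second elevated BP) and Section E (third or later elevated BP).

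**The concern.** A measure that counts diagnoses needs a place to record a diagnosis for every child in its denominator. Here the form stops early for children whose two methods agree, and some of those agree on a hypertensive stage. Protocol section 3 says HBPM is being studied for confirming BP elevation and diagnosing hypertension, so these children are central to the question.

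If their diagnoses go unrecorded, the reported percentage rests mainly on discordant children who accepted further testing. It would then understate how often the pathway ends in a diagnosis. A smaller worry concerns the first measure, because H3 asks about a clinic visit for repeat BP rather than about the device.

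**Working it through.** **1. Which children have a diagnosis field.** Section 3 draws the children from those with one prior elevated BP, and the BP-CATCH 2.0 form excludes anyone with a repeat BP visit since. An elevated reading at the return visit therefore falls in Section D of the earlier tool. There, item 6 asks about Stage II range at this visit, 6a asks about Stage II range at the prior visit, and 6b asks about a documented Stage II diagnosis. A No at 6 or 6a skips 6b, and the rest of Section D has no other diagnosis item. Stage I and elevated-BP diagnoses are asked only in Section E.

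| Child with home data | BP-CATCH 2.0 form | Earlier tool at return visit | Diagnosis field |
|---|---|---|---|
| Discordant, accepts at K2 | reaches K8 | not needed | yes |
| Discordant, declines at K2 | ends at K2 | D6b only if Stage II range at both office visits | only in that case |
| Concordant, Stage II range at both office visits | ends at K1 | D6b | yes |
| Concordant, Stage II range at one office visit only | ends at K1 | skips D6b | no |
| Concordant, Stage I range | ends at K1 | skips D6b | no |

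The two rows marked no, and most of the K2 decliners, can be picked up only if the child later has a third elevated visit entered in Section E. That visit is not part of the HBPM pathway.

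**2. Size.** The Protocol gives no figure to reproduce: no concordance rate, no diagnosis rate, and (section 6.3) no pre-study power analysis for this phase. What follows uses assumed inputs. Section 3 expects home data from 100 children; its 20 per site at six sites would give 20 × 6 = 120. The percentages below hold for either number.

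Let c be the concordant share of children with home data, pC and pD the shares diagnosed among concordant and discordant children, and s the share of diagnosed concordant children that item D6b records. For simplicity, assume nobody declines at K2.

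- True percentage = c·pC + (1 − c)·pD
- Recorded percentage = (1 − c)·pD + s·c·pC
- Shortfall = c·pC·(1 − s)

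With pC = pD = 20% the true value is 20%:

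| c | Recorded if s = 0 | Shortfall if s = 0 | Shortfall if s = 1 |
|---|---|---|---|
| 30% | 0.70 × 20% = 14% | 6 points | 0 |
| 50% | 0.50 × 20% = 10% | 10 points | 0 |
| 70% | 0.30 × 20% = 6% | 14 points | 0 |
| 90% | 0.10 × 20% = 2% | 18 points | 0 |

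The s = 0 column is what the BP-CATCH 2.0 form gives by itself. The continuing tool makes s larger than 0 by an unknown amount. The Protocol supplies none of c, pC, pD or s, so the shortfall cannot be estimated; only its direction is known.

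**3. A narrower denominator does not repair it.** Take c = 50%, pC = 40%, pD = 20% and s = 0. The truth is 0.5 × 40% + 0.5 × 20% = 30%. The recorded figure is 10% of all children with home data, or 20% of discordant children. The discordant-only figure is right only if pC = pD.

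**4. Device refusal.** After H3, the form records the clinic visit date (H4), the office readings and HBPM teaching (Section I), the date the device was received (J1), and whether home data came back (J4). A family that attends without taking a device shows as H4 filled and J1 blank. No item says whether the device was declined or not supplied.

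**The case against.** The strongest reply is that BP-CATCH 2.0 is an add-on. Its sections start at H, following Sections A to G of the earlier tool, and both forms carry a REDCap record ID. Section 5 keeps the earlier outcomes, and the Data and Safety Monitoring Plan says the previously described data will be collected for these patients. The return visit is required by the design, and Section D accepts any visit made for BP follow-up. This stands, and it limits the point. A reader of Section K alone might infer that every concordant hypertensive child, including the most clearly hypertensive, is lost. The documents do not support that, because children in the Stage II range at both office visits have item D6b.

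A second reply is that agreement on a hypertensive stage is not a diagnosis. Section 1.2 describes three sequential office visits and says current guidelines do not endorse HBPM for diagnosis. This also stands. One might be tempted to treat every concordant hypertensive child as diagnosed and quote a large gap, but the Protocol nowhere equates the two. BP stage could be derived for concordant children from recorded readings, age, height and sex. A derived stage still does not show whether a clinician made a diagnosis, which is what the measure counts.

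Third, a reader might infer that the first measure cannot be computed. That goes too far. Section 3 invites families to return to obtain the monitor, and section 5 speaks of agreeing to come in for it, so No at H3 is a reasonable record of refusal. Attendance without a device can be identified. Only the reason is uncoded.

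Finally, this is a descriptive pilot, and the derivation and denominator could be set in an analysis plan. Such a plan can define a measure, but it cannot supply a field that was never collected.

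**Conclusion.** The point holds as a data-capture gap in one listed measure of the new phase's primary outcome. With the forms followed as written, concordant children in the Stage I range, or in the Stage II range at only one office visit, have no field for a diagnosis made. The same is true of those who decline at K2, unless D6b applies to them. The diagnosed percentage is therefore biased downward to the extent that such children are diagnosed.

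The size is not known. The 0 to 18 point range rests on an assumed 20% diagnosed in both groups, a concordant share of 30% to 90%, and anything from none to all of the diagnosed concordant children being recorded by D6b. The conclusion also assumes that no unlisted source, such as an additional chart review, supplies the missing diagnoses. The indirect recording of device refusal is minor. Nothing here bears on clinical management.

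**What to change.** Put a diagnosis item ahead of the stop at K1: diagnosis documented yes or no, date, and basis (office plus home readings, ambulatory monitoring, or nephrology). Complete it for every child with home data, and state that all such children form the denominator. Look back through the charts of children already entered.

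As a lesser change, add one item after Section I recording the device as offered, accepted or declined, so that the first measure is recorded directly.

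The cost is two extra REDCap fields and a short look-back.
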